# De-implementation strategy to reduce unnecessary antibiotic prescriptions for ambulatory HIV-infected patients with upper respiratory tract infections in Mozambique: a study protocol of a cluster randomized controlled trial

**DOI:** 10.1186/s13012-024-01382-8

**Published:** 2024-07-16

**Keywords:** Antimicrobial stewardship, Acute respiratory infections, Protocol, Implementation science, De-implementation, Clinical decision support tool, HIV, Mozambique

## Abstract

**Background:**

Antibiotics are globally overprescribed for the treatment of upper respiratory tract infections (URTI), especially in persons living with HIV. However, most URTIs are caused by viruses, and antibiotics are not indicated. De-implementation is perceived as an important area of research that can lead to reductions in unnecessary, wasteful, or harmful practices, such as excessive or inappropriate antibiotic use for URTI, through the employment of evidence-based interventions to reduce these practices. Research into strategies that lead to successful de-implementation of unnecessary antibiotic prescriptions within the primary health care setting is limited in Mozambique. In this study, we propose a protocol designed to evaluate the use of a clinical decision support algorithm (CDSA) for promoting the de-implementation of unnecessary antibiotic prescriptions for URTI among ambulatory HIV-infected adult patients in primary healthcare settings.

**Methods:**

This study is a multicenter, two-arm, cluster randomized controlled trial, involving six primary health care facilities in Maputo and Matola municipalities in Mozambique, guided by an innovative implementation science framework, the Dynamic Adaption Process. In total, 380 HIV-infected patients with URTI symptoms will be enrolled, with 190 patients assigned to both the intervention and control arms. For intervention sites, the CDSAs will be posted on either the exam room wall or on the clinician´s exam room desk for ease of reference during clinical visits. Our sample size is powered to detect a reduction in antibiotic use by 15%. We will evaluate the effectiveness and implementation outcomes and examine the effect of multi-level (sites and patients) factors in promoting the de-implementation of unnecessary antibiotic prescriptions. The effectiveness and implementation of our antibiotic de-implementation strategy are the primary outcomes, whereas the clinical endpoints are the secondary outcomes.

**Discussion:**

This research will provide evidence on the effectiveness of the use of the CDSA in promoting the de-implementation of unnecessary antibiotic prescribing in treating acute URTI, among ambulatory HIV-infected patients. Findings will bring evidence for the need to scale up strategies for the de-implementation of unnecessary antibiotic prescription practices in additional healthcare sites within the country.

**Trial registration:**

ISRCTN, ISRCTN88272350. Registered 16 May 2024, https://www.isrctn.com/ISRCTN88272350

**Supplementary Information:**

The online version contains supplementary material available at 10.1186/s13012-024-01382-8.

Contribution to the literature
Antibiotic use for acute upper respiratory tract infections is usually unnecessary, as most infections are viral and self-limited. Interventions that promote the de-implementation of this practice will contribute in turn to combat the global threat of antimicrobial resistance.This multicenter cluster randomized controlled trial assesses if a multiprong de-implementation strategy anchored on a clinical decision support algorithm will promote practice change and thus reduce unnecessary antibiotic prescriptions.De-implementation has been understudied in primary healthcare settings in low- and middle-income countries. This study will add to the evidence base around how to de-implement unnecessary antibiotic use in a primary healthcare setting.

## Background

Upper respiratory tract infections (URTIs) are common in adults worldwide [1]. These infections are typically diagnosed clinically based on predominant signs and symptoms and then classified according to their anatomical location such as nasopharyngitis, pharyngitis, tonsillitis, or otitis media [2]. Approximately 90% of all URTIs are of viral etiology and the use of antibiotics may not be indicated [3]. Despite this, as much as 50% to 70% of patients with URTI end up being prescribed antibiotics [4]. Excessive or inappropriate antibiotic use for URTIs is considered a low-value and unnecessary practice and thus needs to be de-implemented [5]. De-implementation is perceived as an important area of research that can lead to reductions in unnecessary, wasteful, or harmful practices [6].

Strategies to promote the de-implementation of unnecessary and wasteful antibiotic use should focus not only on appropriate use but also on the sustainability of behavioral change for both clinicians and patients [7]. Improving antibiotic prescribing requires complementary strategies which include changing clinician behavior and educating patients and families about the role of antibiotics in medical care and their well-being. Commitment to these strategies by clinicians and other relevant health workers may optimize antibiotic prescribing and patient safety. Several studies have recommended appointing a clinical “champion” to promote appropriate antibiotic prescribing [7, 8]. Clinicians who have demonstrated ownership of the process are more likely to be committed to the appropriate use of antibiotics [7].

In high-income countries, several strategies are being employed to promote the de-implementation of unnecessary antibiotic use in patients with URTI across a variety of different clinical settings. These strategies include 1) the use of clinical decision support algorithms (CDSA) by antibiotic prescribers; 2) employment of rapid diagnostic testing or a biomarker to try and reduce uncertainty in diagnosis in real-time, and thus the need for empiric antibiotics; 3) education of healthcare providers, including feedback and auditing concerning their prescribing practices; 4) establishing institutional antibiotic stewardship programs; and 5) creation of, and then deployment of essential medicines policies [9–19].

CDSAs are effective among several strategies to promote the de-implementation of inappropriate prescribing, mainly when combined with the education of health workers [20]. CDSAs have been used in both printed form and within electronic prescribing systems. CDSAs developed for the management of respiratory tract infections have shown significant implementation effectiveness [7]. A considerable number of these tools have been integrated into electronic prescribing platforms and have been associated with reduced inappropriate antibiotic prescribing [7, 11, 21]. In situations in which an electronic platform may not be available, such as in many low- and middle-income countries (LMIC) there is evidence documenting the successful implementation of CDSA in printed form. Rambaud-Althaus et al. evaluated the effect of either a print version of a CDSA or a smartphone-based electronic version and compared it with a control group in a primary healthcare setting. The authors found a significant reduction in antibiotic use in both the printed paper (26%) and electronic CDSA arms (25%), as compared to the control arm (70%) [11].

In persons living with HIV (PLHIV), URTIs are the main reason for an antibiotic being prescribed, especially in those patients with a low viral load [3, 22]. With advances in antiretroviral therapy (ART), the risk of URTIs in PLHIV has reduced over time and is now similar to HIV-uninfected individuals [23]. One exception to this is the HIV-infected patients who quit taking their ART, increasing their vulnerability and risk of getting an infection [24].

## Methods/Design

### Aims and objectives

The overall aim of this study is to evaluate the implementation and effectiveness of a de-implementation strategy for reducing the unnecessary use of antibiotics for the treatment of acute URTIs in HIV-infected adult patients that are being managed in select ambulatory primary healthcare clinics (PHC) in Mozambique. The focus of this evaluation is a multifaceted de-implementation strategy that includes a combination of interventions including health worker education, audit and feedback, organizational adjustments, and the introduction of a CDSA for decision-making around antibiotic use. We subsequently evaluate its implementation and effectiveness as a function of the RE-AIM conceptual framework. The reporting of this protocol adheres to the SPIRIT checklist [28].

### Study setting

This study will be implemented within outpatient primary healthcare clinics in Maputo (the nation’s capital city) and Matola (a city approximately 30 min outside Maputo which is the capital of Maputo Province) municipalities in southern Mozambique. Both municipalities are subdivided into 10 administrative units, hereafter referred to as clusters, containing a total of 31 eligible primary healthcare facilities. All healthcare facilities providing primary care to HIV-infected patients within the study area will be eligible and enlisted for the randomization process.

### Study design and conceptual frameworks

We propose a multicenter two-arm cluster randomized controlled trial that will employ a mixed-methods approach. This study will be guided by two conceptual frameworks, the Dynamic Adaptation Process (DAP) and the Reach, Effectiveness, Adoption, Implementation, and Maintenance (RE-AIM) framework, and will be carried out in three phases (Fig. 1). The DAP framework was developed to provide the structure for an iterative process to guide, monitor, and evaluate the introduction of a new intervention into practice. DAP is a framework that allows changes to be made according to the real context by the possibility of tailoring the elements of the intervention based on data obtained during the pre-implementation and the adaptation. DAP engages stakeholders at all levels to develop robust implementation strategies and will guide the work of phases one, two, and three in our study [29]. *Phase one* (pre-implementation) will consist of a formative baseline evaluation of the current situation for antibiotic prescribing for URTI in the outpatient setting among PLHIV and occur over three months. It will consist of interviews with identified health workers to understand the current antibiotic prescribing practices for URTI among HIV-infected ambulatory patients, as well as perceived facilitators and barriers to the roll-out of our de-implementation strategy. A document review will be performed to identify the existence of national guidelines or normative documents driving antibiotic prescribing for URTI. Phase one will also include documentation of current laboratory diagnostic capacity for URTI and a situational assessment of the availability of medicines to treat URTI. *Phase two* (adaptation and implementation) consists of our de-implementation strategy roll-out and will occur over six months. Based on information learned in phase one, we will make workflow adjustments to address realities on the ground. The CDSA will be rolled out within a two-arm cluster randomized control trial design in which our primary outcome measure will be the clinical decision to use antibiotics or not. Intervention elements and study tools will be adapted before the intervention is implemented. Throughout this phase, an implementation audit and continuous feedback will be conducted to guarantee and monitor adherence to the intervention protocol. *Phase three* (post-implementation) will consist of a three-month post-implementation phase in which we will analyze implementation outcomes and processes as a function of the RE-AIM conceptual framework, in real-time. *Reach* will be assessed in terms of patient recruitment, refusal, and attrition. *Effectiveness* will be analyzed by comparing antibiotic use rates and patient-related clinical outcomes between the intervention and control arms. For *adoption*, clinicians who adopted the practice of de-implementation of unnecessary antibiotic use will be assessed using prescriptions and clinical records. For *implementation*, the fidelity and satisfaction of clinicians regarding the intervention will be assessed. For *maintenance*, sites and clinicians that maintain de-implementation practices and use of the CDSA will be assessed one year after completion of the intervention.

**Fig. 1 Fig1:**
[figure not shown]
The framework of the dynamic adaptation process of the intervention

### Randomization within the two-arm cluster randomized trial and characteristics of the study participants

To mitigate contamination threat to internal validity among participating facilities, randomization and allocation will be primarily among the 10 administrative units (primary clusters). Primary clusters are considered municipal districts (Maputo) or administrative posts (Matola). Randomization will be performed before the initiation of our pre-implementation phase. Initially, randomization will be undertaken through the generation of a sequence of random numbers corresponding to each primary cluster. A total of six primary clusters will be randomly assigned to either the intervention or control arms (three each). Afterwards, in each selected primary cluster only one primary healthcare facility (secondary cluster) will be randomly selected to participate in the study. All participants in the same facility will be assigned to the same treatment, either intervention or control. A statistician will generate the allocation sequence and assign participating healthcare facilities to intervention or control groups.

During phase one (pre-implementation), we will enroll 42 health workers as part of our formative baseline assessment. Eligible health workers will include clinicians, laboratory technicians, pharmacists, and health managers at each of our six study facilities. During phase two (adaptation and implementation), all clinicians at each site working with adult HIV-infected patients aged 18 years and older will be enrolled in the study. Eligible health workers are nurses, clinical officers (called *Técnicos de Medicina* in Portuguese), and physicians. Health workers attending to pediatric patients and those not engaged in the HIV outpatient clinic will be excluded from the study. One identified person (health worker or manager) from each cluster facility will function as a local coordinator, responsible for coordinating activities on site and being the contact between healthcare providers participating in the intervention and the research team. A sample of 380 HIV-infected patients with URTI will be enrolled and assigned to each study arm in a 1-to-1 ratio (190 for each arm) (Fig. 2). To achieve adequate participant enrollment, all clinicians who examine HIV-infected patients in the screening and outpatient consultation rooms at each selected health facility will be requested to identify potential participants among their patients, and the study team will invite them to participate in the study.

**Fig. 2 Fig2:**
[figure not shown]
Study flow diagram: enrollment, intervention, and assessments

For phase three (post-implementation), we will re-interview all clinicians from each of the intervention sites concerning aspects of the intervention implementation and satisfaction.

### Intervention and control

Eligible patients allocated to intervention will be managed using the CDSA. Eligible patients are adult HIV-infected with respiratory symptoms (nasal secretions or runny nose, congestion, sore throat, coughing, sneezing, chills, smell and taste disorders, with or without a fever) [30]. Adult HIV-infected patients without URTI symptoms, those with fever ≥ 39ºC, severe mental illness, or advanced HIV status will be excluded from the study. All PLHIV with URTI symptoms lasting less than 10 days will not receive an antibiotic unless there is an additional symptom suggesting a suspect of bacterial infection. Otherwise, bacterial infection will be suspected in the following situations: (i) higher-grade fever than normally observed with the common cold, with the presence of yellow or greenish nasal discharge, pain/difficulty swallowing, or an intense sore throat; (ii) URTI symptoms lasting longer than 10 days; (iii) URTI symptoms continuing to get worse rather than improve over several days (5 days after the first visit) [31].

Decongestants and/or antihistamines may be used to relieve symptoms of cough, congestion, and runny nose at the clinician's discretion [32]. Those with an increase in symptoms after five days, or a persistence of symptoms after 10 days, without systemic symptoms, will be treated with topical nasal steroids. If improvement of symptoms is observed after five days of treatment with nasal steroids, patients will continue with treatment for seven to fourteen days. Without improvement, consider 5 days of treatment with antibiotics. If improvement, patients should continue with treatment for seven to fourteen days. If symptoms get worse after 5 days of antibiotics, patients will be referred to an ear-nose-throat specialist (ENT). On the other hand, those with systemic symptoms without complications will follow five days of treatment with antibiotics, nasal decongestants, and topical nasal steroids (Fig. 3). Those with complications (acute otitis media, sinusitis, bronchitis, and pneumonia) will be given five days of treatment with antibiotics. Then, without improvement after 5 days of antibiotics, patients will be referred to an ear-nose-throat specialist. The promotion of de-implementation of unnecessary antibiotic use for HIV-infected patients with URTI symptoms lasting less than 10 days will be the core strategy of using the CDSA in the experiment arm.

**Fig. 3 Fig3:**
[figure not shown]
Clinical decision support algorithm

Patients allocated to control will follow usual or routine treatment and will be used as a comparator group. The control arm will allow a fair comparison of the effectiveness of the intervention. No specific intervention will be assigned to the control arm except for follow-up. The clinicians will decide to prescribe medication during each medical visit as they are used to do. For both arms, patients will be enrolled for the first time (t0 = 0 days) and monitored three times (t1 = 5 days, t2 = 10 days, t3 = 15 days) after the initial medical visit to see improvement of symptoms through a phone call, and if necessary, will be asked to visit the healthcare facility for a follow-up clinical examination in person (Fig. 2). If the patient fails to answer the calls at t1, t2, or t3, a home visit on the following day will be made for a follow-up procedure. Participation will be discontinued if the patient’s HIV clinical condition worsens as a result or not of the intervention and appropriate care and treatment will be provided including hospitalization if required.

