Qualitative data will be collected to measure the satisfaction of health workers regarding the implementation of the intervention including information related to adoption and acceptability of the intervention. This data will be collected through in-depth interviews with intervention site clinicians, using an interview guide and will be audio recorded. The interview guide will contain open-ended questions related to the adoption, fidelity, and acceptability of the intervention. An additional survey will be used to assess the degree of clinicians’ satisfaction. Maintenance will be measured as both the number of sites and clinicians that maintain the use of the de-implementation strategy one year after completion of the intervention implementation. This data will be collected from prescriptions and clinical records.

Secondary outcomes consist of the incidence of complications as a result of non-prescription of an antibiotic and the mean time for complete recovery from the first medical visit. This information will be collected from the study data record form. The incidence of complications will be measured as the proportion of complications arising from non-prescription of an antibiotic among patients who did not receive antibiotics. The mean time for complete recovery will be measured as the average time that the patients took to recover completely from their symptoms.

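### The last scheduled contact is day 15, but the algorithm's own steps can put the response and referral decision on day 20, so late complications, referral and recovery have no planned observation

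*Protocol article*

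**What the plan says.** Follow-up is set out in the protocol article, Intervention and control (the text after Fig. 3). In both arms patients are to be "monitored three times (t1 = 5 days, t2 = 10 days, t3 = 15 days) after the initial medical visit". Contact is by phone, with an in-person examination if needed. If a call goes unanswered, "a home visit on the following day will be made for a follow-up procedure", so the latest planned contact is day 16.

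The CDSA steps stand earlier in the same section. Patients whose symptoms increase after five days, "or a persistence of symptoms after 10 days, without systemic symptoms, will be treated with topical nasal steroids". The next decision comes after five days: "If improvement of symptoms is observed after five days of treatment with nasal steroids", steroids continue for a further stated period. Otherwise: "Without improvement, consider 5 days of treatment with antibiotics". Then: "If improvement, patients should continue with treatment for seven to fourteen days". For failure: "If symptoms get worse after 5 days of antibiotics, patients will be referred to an ear-nose-throat specialist".

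Control clinicians prescribe as usual and their patients receive the same calls.

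Under Data collection and measures, the secondary outcomes are complications attributed to not prescribing an antibiotic, and mean time to complete recovery. Of both the article says: "This information will be collected from the study data record form". The complication proportion is taken only over patients who were given no antibiotic. Antibiotic prescriptions, by contrast, come from pharmacy and medical records, with no day limit stated.

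**The concern.** The strategy withholds or defers antibiotics, so its main safety question is what happens to patients who do not settle. The schedule closes on a day when one branch of the algorithm may only be reaching its antibiotic decision. Whether those patients respond, are referred, develop a complication or recover is decided later, when no contact is planned and nothing in the article says how the study form would be completed.

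The article counts patient-related clinical outcomes as part of effectiveness and compares them between arms. If late events go unrecorded more often where antibiotics are deferred, the safety comparison could look more reassuring than it should.

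**Working it through.** The article states the day-15 limit without deriving it, so there is no calculation of the plan's own to reproduce. The check adds up the step durations and compares them with day 15.

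**Inputs** (all from Intervention and control)
- Last contact: day 15, or day 16 after a missed call.
- Steroid start, S: day 5 (worsening) or day 10 (persistence). A problem first found at t3 gives day 15.
- Steroid review and antibiotic decision: A = S + 5.
- Antibiotic response or referral decision: R = A + 5.
- Continued treatment of 7 to 14 days. The text does not say whether this is the total course (end = A + 7 to A + 14) or is added to the first five days (end = R + 7 to R + 14).

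**Counting from the first visit**

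| Branch | S | A | R | End, total reading | End, additional reading |
|---|---|---|---|---|---|
| Worse at t1 | 5 | 10 | 15 | 17-24 | 22-29 |
| Persistent at t2 | 10 | 15 | 20 | 22-29 | 27-34 |
| First found at t3 | 15 | 20 | 25 | 27-34 | 32-39 |

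For the persistent-at-t2 branch, the response decision falls 20 - 15 = 5 days after the last contact. Treatment ends 7-14 days after it (22 - 15 to 29 - 15) or 12-19 days after it (27 - 15 to 34 - 15). On the worse-at-t1 branch the response decision coincides with the last contact, and only continued treatment runs past it.

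**Counting the 10 days from symptom onset**

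Let symptoms begin s days before the first visit. If the rule is acted on at once, S = 10 - s, A = 15 - s and R = 20 - s. R exceeds 15 only when s is below 5, that is s = 0 to 4:
- s = 0: R = 20
- s = 4: R = 16
- s = 5: R = 15

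If the rule is acted on only at scheduled contacts, s = 0 to 4 is picked up at t2 and gives A = 15, R = 20 again. The affected group is the same, patients presenting within about 4 days of onset. Continued treatment can still pass day 15 for some longer onsets (at s = 5, days 17-24 on the total reading), but the response decision does not.

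**Observation left after antibiotics start** (15 - A)
- Started at t0: 15 days
- Worse at t1: 15 - 10 = 5 days
- Persistent at t2: 15 - 15 = 0 days

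These are times from treatment start, which follows allocation. From enrolment, both arms have the same 15 days.

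**The case against.** The best case against this has five parts.

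1. The branch is narrow. It needs no systemic symptoms, persistence past 10 days and no response to steroids, and then a clinician who chooses antibiotics, because the text says only to consider them. This stands: the documents give no rate, so the number of patients affected cannot be stated.
2. The 10-day clock may be symptom duration. The section speaks of symptoms lasting less or more than 10 days, and separately ties worsening to 5 days after the first visit. This stands as a plausible reading. It narrows the affected group but does not empty it.
3. Both arms are observed for the same time from enrolment, and the period during which antibiotics are withheld on this branch, days 0-15, is covered by contacts. This also stands, so the between-arm effect is an inference from the deferral rule.
4. Complications after deferred antibiotics lie outside the complication outcome anyway, since its denominator excludes anyone given an antibiotic, and referral is not a listed outcome. Correct: a longer window alone would not bring them in, so the fix must also deal with the denominator. Late complications in patients never given antibiotics are inside the definition and are still missed.
5. Figs 2 and 3 are not shown, and the article condenses a fuller protocol that may say how patients on treatment at t3 are handled. Possible, but the text states three contacts outright.

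A reader might go further and infer that late antibiotic starts are missed, so that the strategy would look more antibiotic-sparing against its 15-point target. The documents do not support that. Prescriptions come from records without a stated day limit, and a decision on day 15 coincides with a scheduled contact.

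**Conclusion.** The point holds as a mismatch between two parts of one section. The contact schedule ends on day 15, while the algorithm can place the response or referral decision on day 20 and the end of treatment on days 22-29 or 27-34. The day-20 result assumes either that the 10 days run from the first visit, or that they run from onset in a patient presenting within about 4 days of it.

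The consequence is limited. Complications, referral and recovery have no scheduled observation in patients still symptomatic or on treatment at t3. It is reasonable to expect more such patients where antibiotics are deferred, but a reader should not treat loss mainly in the intervention arm as established. Nor are these events certain to go unseen, since patients can be examined in person and records exist. What is missing is planned capture.

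This bears on the secondary safety outcomes. It does not invalidate the primary comparison of antibiotic use.

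**What to change.** Reconcile the follow-up schedule with the algorithm's step durations. State which day the 10-day clock starts from, and whether the 7-to-14-day continuation is the total course or additional. The clinical steps themselves are for the investigators; nothing here requires changing them.

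Keep t1-t3 and add, identically in both arms:
- a records check for every patient to one common closing date, about day 30-35;
- one closing phone contact, preferably for everyone and at minimum for patients symptomatic or on treatment at t3;
- counts of antibiotics, complications, referrals and hospitalisations over that same window;
- complications reported among all enrolled patients in each arm. The present proportion among patients given no antibiotic may be kept as a supplement, but it cannot serve as the safety comparison because it drops those given deferred antibiotics.

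A closing date of day 35 would cover the persistent-at-t2 branch on both readings (latest end day 34). It would also cover the response decision on day 25 for problems first found at t3, though not every possible end of treatment there (up to day 39).

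The cost is at most 380 extra calls through the existing phone system, some non-response and a short amendment. Recruitment began in June 2024, so patients already past follow-up would be covered by records only. The change should start on the same date at all six facilities, so that capture does not differ by arm.

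### Ending participation when HIV disease worsens also ends outcome collection, so later complications and unfinished recovery go unrecorded for a probably small but informatively selected group

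*Protocol article*

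**What the plan says.** All references are to the protocol article.

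- **Discontinuation rule** (Intervention and control, paragraph on follow-up in both arms). The condition for ending participation reads: "HIV clinical condition worsens as a result or not of the intervention and appropriate care and treatment will be provided". Hospital admission is named as part of that care where needed. What ends is participation, not use of the algorithm.
- **Content of control-arm participation** (same paragraph). "No specific intervention will be assigned to the control arm except for follow-up".
- **Schedule** (same paragraph). Patients in both arms are "monitored three times (t1 = 5 days, t2 = 10 days, t3 = 15 days) after the initial medical visit".
- **Retention** (same paragraph). "If the patient fails to answer the calls at t1, t2, or t3, a home visit on the following day will be made". This covers unanswered calls. Nothing is said about patients who have been discontinued.
- **Outcomes exposed to the rule** (Data collection and measures). "Secondary outcomes consist of the incidence of complications as a result of non-prescription of an antibiotic and the mean time for complete recovery". Both are taken from the study data record form. Complications are expressed as a proportion of patients who received no antibiotic; recovery is the "average time that the patients took to recover completely from their symptoms".
- **Use of these outcomes** (Study design and conceptual frameworks). Effectiveness includes comparing patients' clinical outcomes between arms. Drop-out is counted only as part of Reach.

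**The concern.** Worsening of HIV disease happens after randomization, and the rule applies whether or not the intervention caused it. The plan therefore foresees that the intervention could contribute to the event, and then ends observation of the patients in whom it occurs.

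The two secondary outcomes are the clinical endpoints that the article sets against a strategy of withholding antibiotics. If patients who deteriorate leave follow-up, later complications are not counted, and a recovery that had not finished adds nothing to the mean. Loss of this kind depends on prognosis. If the intervention contributes to worsening, more of it falls in the intervention arm, and the strategy would look safer than it is.

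**Working it through.** The article states no complication, recovery or discontinuation rate, so there is no figure to reproduce. The first step is textual; the second uses assumed rates to show direction and range.

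**1. Does ending participation end outcome collection?** In the control arm no study management is assigned, only follow-up, so stopping participation there can only mean stopping follow-up. The rule is worded identically for both arms. The home visit is triggered by a missed call, which presupposes that calls are still being made. No other section restores the contacts for discontinued patients. As written, collection stops.

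**2. Which outcomes are touched?**
- The antibiotic decision is largely made at the first visit, so it is little affected.
- A complication seen at or before discontinuation can already be on the form, and nothing in the article discards it.
- Complications after discontinuation, and recovery not yet reached, are lost.

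**3. Complication risk (assumed rates).** Let p be the true risk among patients without antibiotics, and d the share of complications that go unrecorded because the patient was discontinued first. Among those retained:

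observed risk = p(1 − d) / [p(1 − d) + (1 − p)]

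| True p | d = 10% | d = 25% | d = 50% |
|---|---|---|---|
| 5% | 4.5% | 3.8% | 2.6% |
| 10% | 9.1% | 7.7% | 5.3% |

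Example: p = 5%, d = 50% gives 0.025 / (0.025 + 0.95) = 2.6%.

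**4. Comparison between arms (assumed true risks 10% intervention, 5% control, ratio 2.0).**

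| d, intervention | d, control | Observed risks | Observed ratio |
|---|---|---|---|
| 25% | 25% | 7.69% v 3.80% | 2.03 |
| 50% | 50% | 5.26% v 2.56% | 2.05 |
| 40% | 10% | 6.25% v 4.52% | 1.38 |
| 50% | 10% | 5.26% v 4.52% | 1.16 |

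Equal loss lowers the absolute risks but hardly moves the ratio. Only unequal loss distorts the comparison.

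**5. Recovery time (assumed).** Suppose a share s of patients needs 15 days, the last planned contact, and the rest average 7 days. The full mean is 15s + 7(1 − s): 7.16 days for s = 2%, 7.40 for s = 5% and 7.80 for s = 10%. If the slow group is discontinued before recovery, the observed mean is 7.0 in each case.

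**The case against.** **The trigger is not the outcome.** The rule names worsening of the HIV condition, which is undefined, and not worsening of the respiratory infection. Worsening or persisting respiratory symptoms, the named complications and specialist referral all have pathways inside the study. A reader might infer that the rule removes the patients who develop complications or recover slowly. The document does not say that. The overlap is a reasonable inference; its only support in the article is a remark in the Background that patients who stop antiretroviral therapy are more vulnerable to infection. This part of the objection stands.

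**Few patients are likely to be affected.** Advanced HIV is an exclusion and follow-up is 15 days. This stands too.

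**The size can be overstated.** A reader might calculate that most of a safety signal disappears. With a true risk of 5%, 5% of patients discontinued and 60% of those having a complication, the observed risk is (0.05 − 0.05 × 0.6) / 0.95 = 2.1%. With 3% discontinued it is (0.05 − 0.03 × 0.6) / 0.97 = 3.3%. The arithmetic is right, but it assumes that every complication in a discontinued patient goes unrecorded and places 60% (0.03 / 0.05) or 36% (0.018 / 0.05) of all complications in that group. It also treats the risk as one for the whole arm, whereas the outcome is defined only among patients without antibiotics. Nothing in the document supports those inputs.

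**A condensed article may leave this to a fuller document.** Handling of missing data can be left to an analysis plan, and its absence here is not criticized. But the point rests on a rule that is stated, and no analysis method recovers outcomes that staff were told to stop collecting. This objection does not remove the point.

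**Conclusion.** The point holds in a limited form. The stated rule ends follow-up, in both arms, after a post-randomization event that the intervention may influence. Later complications and unfinished recovery times are lost for those patients, and the loss is informative.

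Its size cannot be derived from the document. The figures above show what assumed rates would do; they are not estimates for this trial. Absolute complication risks and mean recovery time would be understated if the discontinued patients do worse than the rest. The comparison between arms would be materially distorted only if loss differed clearly by arm, which is possible but not shown. The primary conclusion on prescribing is not in question. This is an inexpensive improvement to the secondary clinical outcomes, not a defect that undermines the trial.

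**What to change.** Leave the sentence on clinical care and hospitalization unchanged, and separate leaving study management from leaving follow-up. One added statement is enough: stopping study management for any reason does not end follow-up; the patient stays in the assigned arm, the remaining t1, t2 and t3 contacts are completed (or replaced by record review if the patient is hospitalized), and the data count in the outcomes unless consent is withdrawn. Align the study data record form, with the date of and reason for stopping, so that any imbalance between arms can be seen.

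**Cost.** A short amendment to a trial that is already recruiting at all sites, a form revision and a few extra contacts. Calls and home visits are already planned. Because each patient's follow-up window is only 15 days, outcomes missed before the change may be hard to recover, so it is better made early.
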